Appendix 2 Pegasys Dose Adjustment Guidelines [35](#__RefHeading___Toc122877008)

Appendix 3 Copegus Intended Dose and Dose Adjustment Guidelines 38

Appendix 4 Intervention Guidelines in the Event of Anemia 41

Appendix 5 Instructions for Sample Processing and Shipment for RibaC 42

| Glossary Of Abbreviations | |
| --- | --- |
| Ab | Antibody |
| AE | Adverse event |
| AFP | Alpha-1-fetoprotein |
| Ag | Antigen |
| ALT (SGPT) | Alanine aminotransferase |
| a1 AT | Alpha 1 antitrypsin |
| AMA | Anti-mitochondrial antibodies |
| ANA | Anti-nuclear antibodies |
| AP | Alkaline phosphatase |
| AST (SGOT) | Aspartate aminotransferase |
| ASMA | Anti-smooth muscle antibodies |
| b.i.d. | Twice daily |
| BP | Blood pressure |
| CHC | Chronic hepatitis C |
| CI | Confidence interval |
| CMV | Cytomegalovirus |
| CRF | Case Report Form(s) |
| DNA | Deoxyribonucleic acid |
| ECG | Electrocardiogram |
| EOT | End of Treatment |
| HAV | Hepatitis A virus |
| HBc | Hepatitis B core |
| HbsAg | Hepatitis B surface antigen |
| HCV | Hepatitis C virus |
| HIV | Human immunodeficiency virus |
| ICH | International Conference on Harmonization |
| IDB | Investigational Drug Brochure |
| IEC | Independent Ethics Committee |
| Glossary Of Abbreviations (cont’d) | |
| IFN | Interferon alpha |
| IRB | Institutional Review Board |
| IgM | Immunoglobulin M antibody |
| IPT | Interferon gamma inducible protein |
| ITT | Intent to treat |
| MIU | Million International Units |
| MRI | Magnetic Resonance Imaging |
| mRNA | Messenger ribonucleic acid |
| OAS | 2’5’-Oligoadenylate synthetase |
| PCR | Polymerase chain reaction |
| PEGASYS® | Pegylated-Interferon-alpha-2a 40 KD |
| RBV | Ribavirin |
| RNA | Ribonucleic acid |
| RBC | Red blood count |
| SAE | Serious adverse event |
| Sc | Subcutaneous |
| SVR | Sustained Virological Response |
| Tiw | Three times per week |
| T4 | Thyroxin |
| TSH | Thyroid-stimulating hormone |
| ULN | Upper limit of normal |
| WBC | White blood count |
| VRVR | Very Rapid Virologic Response |
| RVR | Rapid Virologic Respose |
| cEVR | Complete Early Virologic Response |
| pEVR | Partial Early Virologic Response |

# Part I: Study design and conduct

# background and rationale

## Background

Hepatitis C virus (HCV) accounts for approximately 70% of cases of chronic hepatitis in industrialized countries. If left untreated patients may develop cirrhosis, end-stage liver disease, portal hypertension and hepatocellular carcinoma (1, 2).

The response to therapy is greatly related to HCV genotype. Seven genotypes of HCV have been currently been identified. Genotype 1 (G1) is the most common in the Nordic countries, and occurs in approximately 40-50% of cases. Genotypes 2 and 3 (G2/3) contribute an additional 40-50%, and genotypes 4-7 constitute the remaining 5%.

## Study Medications

The current recommended treatment for patients with chronic hepatitis C (CHC) is the combination of Pegylated interferon-alfa (PEG-IFN) and ribavirin (RBV) (3). Interferon-alfa was the first drug shown to have bioactivity against HCV. Combining RBV with interferon-alpha was found to be more effective than interferon-alpha monotherapy in previously untreated patients as well in patients who relapsed after one or more courses of interferon-alpha therapy (4).

### PEGASYS® (Peginterferon-alpha-2a, PEG-IFN 2a)

The interferon-alpha-2a molecule has been chemically modified by Hoffmann-La Roche with a covalent attachment of a branched methoxy polyethylene glycol moiety (5). PEGASYS® (Peginterferon-alpha-2a, PEG-IFN alfa 2a) has a decreased systemic clearance rate and an approximately 10-fold increase in serum half-life compared with interferon-alpha-2a, so that PEGASYS circulates in the blood much longer than does the parent compound. The biological activity of PEGASYS, as measured using serum 2’5’-oligoadenylate synthetase (OAS) activity, is similarly prolonged, resulting in a significantly improved pharmacodynamic profile compared with that of interferon. These observations and additional pharmacokinetic and pharmacodynamic data obtained from animals and healthy male volunteers suggested that PEGASYS injected once per week might be more efficacious than interferon injected three times per week (tiw) (6). Indeed, this hypothesis was confirmed in three large clinical trials in over 1400 patients where treatment with PEGASYS 180 µg once weekly was shown to be more efficacious than treatment with interferon-alpha-2a thrice weekly (5).

### Copegus® (Ribavirin)

Copegus® (RBV) is a guanosine analogue that inhibits the in vivo replication of a wide range of RNA and DNA viruses (7). The mechanism of antiviral activity is not fully defined, although it may involve alteration of cellular nucleotide pools and inhibition of viral RNA synthesis (8). RBV monotherapy has little effect on the replication of HCV but can result in normalization of serum ALT activity and improvement in liver histology. However, relapse occurs in nearly all patients treated with RBV alone (9, 10).

Combining Copegus with PEGASYS has been found to be more effective than PEGASYS monotherapy in the treatment of CHC (5). In a large clinical trial of 1121 patients, a sustained virological response (SVR) was achieved in 53% of patients treated with PEGASYS plus Copegus as compared to 29% of patients treated with PEGASYS alone.

## Clinical Experience

### Combination therapy of Peginterferon-alpha-2a and Ribavirin

The safety and efficacy of PEGASYS in combination with COPEGUS for treatment of hepatitis C infection were assessed in two randomized controlled clinical trials (11, 12). Based on the results of these trials, PEGASYS in combination with COPEGUS is indicated for treatment of adults with chronic hepatitis C infection who have compensated liver disease. It has long been recognized that patients with hepatitis C virus (HCV) genotype 2 or 3 respond better to interferon (IFN) treatment than patients infected with HCV genotype 1, and that patients achieving higher ribavirin concentrations are more likely to achieve SVR (13). Additionally it has recently been reported that higher ribavirin concentrations already on the first day of therapy is associated with improved outcome (14).

## Rationale

### Rationale for the Study Design

Recently it has been reported that higher ribavirin concentrations as early as the first day of combination therapy for HCV as well as higher that standard dosing of ribavirin is associated with improved outcome (18). Additionally because of the long half-life of ribavirin, it takes greater than 4 weeks to achieve steady-state concentrations. In this pilot study, we will evaluate two potentially new strategies to achieve higher initial ribavirin concentrations. The first strategy entails giving a higher initial dose of ribavirin during the first two weeks (“loading”) similar to current clinical practice for many antibiotics. Moreover, a ribavirin concentration after 4 weeks of therapy will be available to the treating physician, enabling possible dose adjustments in the event of suboptimal concentrations. The second strategy encompasses giving mono-therapy with ribavirin for 4 weeks prior to initiating therapy with pegylated interferon (“priming”). In this treatment arm a ribavirin concentration after 4 weeks will also be available as in Group A above. Both of these strategies will be compared to a control group receiving standard-of-care dosing of ribavirin, where no ribavirin concentration is available during therapy as is often the case in current clinical practice.

### Viral kinetics

A large combination trial including 1121 patients, with 453 patients receiving PEGASYS 180 µg/ week and 1000-1200 mg Copegus, with a treatment duration of 48 weeks was the first study to show that a virological response at week 12, defined as a 2-log decrease from base-line HCV-RNA levels or no detectable serum HCV RNA, is a strong predictor of a SVR (11). In this study 86 % of the patients had an early virological response and subsequently 65 % of these patients went on to have a SVR response. Ninety-seven percent (97 %) of patients with HCV genotype 2/3 had an early virological response and 77 % of these patients became a SVR.

There have also been studies looking into rapid virological response at week 4 as a predictor of sustained virological response. In a large combination trial including 1284 patients with chronic hepatitis C, patients received PEGASYS 180 µg/ week in combination with 800 or 1000-1200 mg Copegus per day for 24 or 48 weeks (12). 94% of the patients with HCV genotype 2/3 had a virological response by week 4, and 87 % of these patients had a SVR as compared to 17% SVR for the patients without a virological response by week 4.

In this study, HCV-RNA levels in plasma during the first 12 weeks of therapy will be utilized to evaluate the efficacy of therapy in the 3 treatment arms.

### Liver Fibrosis and Inflammation Score

Liver biopsy is currently considered the gold standard for assessing liver necroinflammation and fibrosis in patients with CHC. It is though a costly an invasive procedure with a risk of complications (15) and the risk of sampling error (16). In a recent retrospective, single-center study by Islam *et al.* (17) a novel index, normalized aspartate amininotransferase (AST), PK-INR, and platelet count (Gothenburg University Cirrhosis Index; GUCI), in predicting liver fibrosis and cirrhosis was introduced. The index uses objective routine laboratory data and is calculated using a simple formula. GUCI is reported to accurately exclude the likihood of cirrhosis if this index is below 1.0. Since liver biopsies will be encouraged but not mandatory in this trial, GUCI will be used as a marker of the fibrosis stage to stratify patients. If a liver biopsy within 2 years of initiation of therapy in this trial has been obtained, central staging of fibrosis and grading of inflammation and steatosis will be performed.

### Rational for Dosage Selection

#### Pegasys

The dose chosen for PEGASYS® (180 g, sc, once per week) is the dose currently approved in EU for combination therapy with COPEGUS (5).

#### Ribavirin

The dose chosen for COPEGUS 13 mg/kg body weight/day is based on the current Swedish National Treatment Guidelines, and is the current standard of care in Sweden for HCV genotype 1 infected patients (18). Patients in Group A (“Loading”) will receive a double dose the first 2 weeks of combination therapy followed by standard 13 mg/kg body weight/day. And patients in Group B (“Priming”) will receive standard 13 mg/kg body weight/day dosing of ribavirin for four weeks prior to initiating pegylated interferon, which will be maintained during the ensuing 48 week treatment period. Ribavirin should be administered twice-daily with food.

# OBJECTIVES OF The STUDY

## Primary Objective

To evaluate the efficacy of (A) 2 weeks of high dose of ribavirin (“loading”, ≥26 mg/kg/day for 14 days followed by ≥13 mg/kg/day) vs. (B) 4 weeks of ribavirin dosing before initiation of PEG-interferon dosing (“priming”, ≥13 mg/kg/day) followed by concentration targeted (≥ 2.5 mg/L (10.25 μmol/L) 28 days after initiation of ribavirin therapy) dosing of ribavirin in combination with peginterferon alpha-2a in interferon naïve patients with chronic hepatitis C (CHC) virus genotype 1 infection as compared to (C) standard-of-care dosing of ribavirin (≥13 mg/kg/day without monitoring of ribavirin concentrations) in combination with peginterferon alpha-2a as evaluated by the early viral kinetic response and SVR measured by effect on the initial decline of HCV-RNA (during the first days after initiating peginterferon and ribavirin therapy) and second phase decline (day 7 to week 12 of therapy).

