| TRIAL DESIGN | Multicenter, randomized, open-label, parallel group pilot study.  Randomization to the three treatment arms A, B and C will be stratified by gender, age above or below 40 years, and presence of liver cirrhosis/non-cirrhosis (as evaluated by the Gothenburg University Cirrhosis Index (GUCI) 1.0). | | |
| DISCONTINUATION SCHEME | Treatment will be stopped in patients having a decline of HCV-RNA less than 2-log10 after 12 weeks or detectable HCV-RNA after 24 weeks of study treatment as measured by Roche COBAS AmpliPrep/COBAS TaqMan HCV Test (≤15 IU/mL) | | |
| NUMBER OF SUBJECTS | Total of 105 patients, 35 per treatment group. | | |
| TARGET POPULATION | Men and women >18 years old with CHC genotype 1 will be enrolled in this study. Patients must have quantifiable HCV-RNA, and must have compensated liver disease (Child-Pugh Grade A). Liver biopsies and/or FibroScan evaluations are encouraged especially for patients with a Gothenburg University Cirrhosis Index (GUCI, a cirrhosis index calculated by (normalized AST x PK-INR x 100) / Platelet count (x 109/L)) 1.0, but not mandatory. Patients with other forms of liver disease, human immunodeficiency virus (HIV) infection, hepatocellular carcinoma, anemia, pre-existing severe depression or other psychiatric disease, significant cardiac disease, renal disease, seizure disorders, or severe retinopathy, or previously treated with interferon/ peg-interferon with or without ribavirin are excluded. | | |

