# end points of the study

## Primary Endpoint

The early virological response as measures by the decline in HCV-RNA during the first 12 weeks (in particular the first and second phase decline) of peginterferon alpha-2a and ribavirin therapy in the three study arms.

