## Percentage of patients with non-detectable HCV-RNA at study day 1, 3, 7, 14, 21, 28, week 8, week 12, end of treatment, and 24 weeks after completion of treatment as measured by TaqMan PCR as compared to day 0.

## SVR rate defined as percentage of patients with non-detectable HCV-RNA as measured by TaqMan PCR at 24 weeks post completion of the treatment period in the three study arms.

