#### Interim Analysis

# An independent DSMB will evaluate safety after the first 30 patients have reached treatment weeks 2 and 12.

## Sample Size

This is a pilot trial with the viral kinetic response and SVR measured as described above, during the first 12 weeks of therapy as primary endpoint with the aim of investigating the feasibility and safety of “loading” and “priming” dosing of ribavirin in conjunction with PEG-IFN for chronic HCV genotyp 1. To demonstrate an increase in the reduction of HCV RNA from day 0 to 3 from 0.9 log10 IU/mL in Group C (Standard-of-Care) to 1.4 log10 IU/mL in Group A or B or an increase in the reduction of HCV RNA from day 7 to 28 from 0.4 log10 IU/mL/week in Group C (Standard-of-Care) to 0.6 log10 IU/mL/week in Group A or B the study requires at least 35 patients per study arm. The statistical power (chance) for the study to detect a superior effect in Group A or B as compared to C is 80%. Statistical sample-size calculation is based on z-test for differences between proportions and is one-sided with a significance level of 5%.

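### The primary objective runs the second-phase decline from day 7 to week 12, but the sample size and its 80% power rest on day 7 to 28; over the longer window the 15 IU/mL limit can strongly shrink the sized contrast

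*Protocol*

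**What the plan says.** The primary objective (Section 2.1, and the synopsis under Objectives) names two components of early viral kinetics: an initial fall over the first days and a "second phase decline (day 7 to week 12 of therapy").

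The sample size (Section 9.3, and the synopsis under Statistical Analyses) uses other limits for the second component. It plans for a "reduction of HCV RNA from day 7 to 28 from 0.4 log10 IU/mL/week in Group C (Standard-of-Care) to 0.6 log10 IU/mL/week in Group A", with the same figure for the priming arm. This is joined by *or* to a first-phase effect, a "reduction of HCV RNA from day 0 to 3 from 0.9 log10 IU/mL in Group C (Standard-of-Care) to 1.4 log10 IU/mL in Group A", which likewise applies to the priming arm. From these it derives 35 patients per arm with 80% power.

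Section 6.1 defines the primary endpoint as the "decline in HCV-RNA during the first 12 weeks (in particular the first and second phase decline"), without day limits for either phase. Section 9.1.1 does the same, so neither settles which second-phase window is primary.

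The stated HCV-RNA limit is in the synopsis under Discontinuation Scheme: "Roche COBAS AmpliPrep/COBAS TaqMan HCV Test (≤15 IU/mL"). Section 5.3.1 (Viral Kinetic) lists central-laboratory HCV-RNA in the second phase at day 7, day 28 and week 12 only. The week-12 sample is therefore the end value of the longer window.

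**The concern.** Two different variables carry the same name in one component of the primary endpoint. The power statement belongs to the 3-week version and the objective to the 11-week version. They would be interchangeable only if a slope measured to week 12 estimated the same contrast as a slope measured to day 28.

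At the protocol's own rates it need not. Over 11 weeks the virus would fall below what the assay can measure in many patients, and sooner in the arms where treatment works better. The cEVR endpoint shows that undetectable week-12 results are expected. If such values enter as if observed, the fall from day 7 is capped, and the cap is lower where the first-phase fall was larger.

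At stake is whether the second-phase comparison has anything like the stated power. There is also a question of timing. The trial is open-label and the synopsis plans an analysis of the primary endpoints once all patients have reached week 12. With two windows in the text, the choice could be made after data are seen.

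**Working it through.** **1. The plan's own figure.** Section 9.3 names a "z-test for differences between proportions and is one-sided with a significance level of 5"%, but its inputs are log10 means and no SD is given. Treating them as means, n = 2(1.645 + 0.842)² SD²/δ². With n = 35 this gives SD = δ × √(35/12.37) = 1.682 δ:
- slope, δ = 0.2/week: SD = 0.336 log10/week;
- day 0 to 3, δ = 0.5: SD = 0.841 log10.

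These are the SDs that 35 per arm implies. They are back-solved, not stated, so 35 is neither confirmed nor refuted.

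**2. Falls at the planned rates.**
- Day 7 to 28 (3 weeks): 0.4 × 3 = 1.2 (C) and 0.6 × 3 = 1.8 (A or B); difference 0.6 log10.
- Day 7 to week 12 (11 weeks), if the rate stays constant: 4.4 and 6.6; difference 2.2 log10.

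**3. The floor for one typical patient.** Floor = log10(15) = 1.18. Observed fall = min(slope × weeks, day-7 level − 1.18), with day-7 level = baseline − first-phase fall. Assumed: no further fall from day 3 to day 7, and undetectable set to 15 IU/mL. At an assumed baseline of 6.0:
- C: 6.0 − 0.9 = 5.1, room 3.92, floor reached after 3.92/0.4 = 9.8 weeks;
- A: 6.0 − 1.4 = 4.6, room 3.42, floor reached after 3.42/0.6 = 5.7 weeks.

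Both times lie inside 11 weeks, so the observed falls are 3.92 and 3.42. Over day 7 to 28 they are 1.2 and 1.8, as planned. Observed A minus C over day 7 to week 12 (planned +2.2 log10):

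| Baseline, log10 | Both effects present | Second-phase effect only |
|---|---|---|
| 6.0 | −0.50 | 0.00 |
| 6.5 | −0.48 | +0.02 |
| 7.0 | +0.02 | +0.52 |

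**4. With between-patient spread.** Simulation of 20,000 trials per row: 35 per arm, one-sided 5% t-test, normal distributions, baseline SD 0.7, first-phase SD 0.841, undetectable set to 15 IU/mL. The baseline means, baseline SD and slope SDs are assumptions. True slope difference 0.20/week.

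| Effects | Slope SD | Mean baseline | Day 7–28: difference, power | Day 7–week 12: difference, power | At floor, week 12 (C, A) |
|---|---|---|---|---|---|
| Both | 0.2 | 5.5 | 0.165, 96% | 0.000, 5% | 65%, 93% |
| Both | 0.2 | 6.5 | 0.193, 99% | 0.029, 26% | 50%, 86% |
| Both | 0.336 | 5.5 | 0.150, 64% | 0.023, 14% | 60%, 83% |
| Both | 0.336 | 6.5 | 0.186, 76% | 0.045, 27% | 50%, 76% |
| Second only | 0.2 | 5.5 | 0.188, 99% | 0.041, 48% | 65%, 90% |
| Second only | 0.2 | 6.5 | 0.197, 99% | 0.067, 78% | 49%, 81% |
| Second only | 0.336 | 5.5 | 0.180, 77% | 0.059, 46% | 60%, 80% |
| Second only | 0.336 | 6.5 | 0.196, 79% | 0.078, 56% | 50%, 71% |

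At a mean baseline of 7.0 with both effects, the longer window gives 34 to 47% against 78 to 99%. The rows with SD 0.336 are the ones consistent with 35 per arm; an SD of 0.2 would give about 99% power over day 7 to 28, not 80%.

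**The case against.** Several counter-arguments have force.

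- **The attenuation needs an analysis rule that the protocol does not state.** It arises if undetectable values are treated as observed, and the SAP, which is not at hand, may do otherwise. This stands. In a check with both effects present and the day 7 to week 12 window kept, a censored normal model gave a median difference of about 0.19 to 0.20/week, with power from roughly 60% to just over 90%. It was unstable in some replicates where over 90% of one arm was at the floor. It also leans on a constant slope to week 12.
- **The inputs are partly outside the document.** The protocol gives a minimum viral load but no mean, and its rates only for day 7 to 28. The 15 IU/mL limit is stated for the discontinuation test, and none is stated for the central kinetic assay. All this stands, so the sizes are conditional.
- **The planned effects are joined by *or*.** With the second-phase effect alone the loss is much milder. The day 0 to 3 comparison is untouched by the floor.
- **Twelve weeks is the recurring time frame of the primary endpoint.** Choosing day 7 to 28 is therefore one of two valid repairs.

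A reader might infer that the longer window generally erases or reverses the benefit. The documents do not support that. Reversal appears only for a typical patient at or below about 6.5 log10 with both effects present. Under the spread assumed above, the difference is about zero at one corner and positive elsewhere.

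A reader might also count ribavirin changes after the day-28 concentration as contamination of the longer window. They are not a defect: concentration-targeted dosing is part of the regimens under test in Groups A and B.

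None of this removes the contradiction. An SAP could only choose one of the two windows.

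**Conclusion.** The point holds. The objective and the sizing define the second-phase component over different windows, in the body and in the synopsis, and the endpoint sections leave it open. That part needs no assumption: the 80% power is not established for the variable in the primary objective.

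The consequence is conditional. It assumes constant rates to week 12, a 15 IU/mL floor, undetectable values analysed as observed, mean baselines of 5.5 to 6.5 log10 and slope SDs of 0.2 to 0.336. The longer window then shows about 0.00 to 0.045/week of a true 0.20 with both effects (power about 5 to 27%), and about 0.04 to 0.08 with the second-phase effect alone (about 46 to 78%). Day 7 to 28 gives about 64 to 99% and 77 to 99%. The description that fits is strong attenuation, less at higher baselines. Being a pilot does not excuse it, because the protocol claims 80% power to detect superiority.

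**What to change.** State one second-phase window, identically, in the synopsis (Objectives and Statistical Analyses) and in Sections 2.1, 6.1, 9.1.1 and 9.3.

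- **Day 7 to 28** matches the sizing: slope in log10 IU/mL per week, with days counted from the first peginterferon dose. Week 12 is then reported through the existing cEVR and pEVR endpoints. The downside is that effects of ribavirin adjustment after day 28 no longer enter the slope, and this should be acknowledged.
- **Day 7 to week 12**, if kept, needs its power restated for that window, with the assumed baseline viral load, SD and share of undetectable values given.

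In either case, state that values below 15 IU/mL are analysed as left-censored (for example a Tobit or censored mixed model), not as observed, and confirm that this limit applies to the central assay.

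The cost is consistent wording in six places and a censored model. No extra visits or samples are needed. Section 6.2 also promises HCV-RNA results at days 1, 14 and 21 and week 8, which the central sampling list does not include; that is a separate point.
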